### Study and participant timeline

The study is planned to be conducted over an estimated twelve-month period. At the time of this submission, the project is in its preparatory phase; no participant recruitment has begun, and no data have been generated. Participant recruitment is expected to commence in October 2026 and to be completed by December 2026. Baseline data collection will be conducted in January 2027. The six-session group intervention will then be delivered over the subsequent weeks. Immediate post-intervention assessments are expected to be completed by March 2027, following completion of the intervention. After a planned six-month interval, follow-up data collection is anticipated to take place in September 2027. Statistical analyses and final results are expected to be completed and ready for dissemination between October and November 2027. This timeline has been designed to ensure feasibility and full compliance with institutional and journal requirements.

The participant timeline is presented in accordance with SPIRIT 2025 recommendations and illustrates the schedule of enrollment, allocation, intervention delivery, and outcome assessments for the trial [20] (Fig 1).

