### Participants’ eligibility

The target population will consist of female university students aged 18–25 years, enrolled in Health Sciences degree programs. This age range was selected because it corresponds to a developmental stage characterized by significant changes in health-related behaviors and increased psychological vulnerability, thus highlighting the relevance of preventive interventions within the university context [4,22].

The focus on Health Sciences students is particularly relevant, as they are future health professionals. Research suggests a ‘motivational spill-over’ effect, where fostering autonomous regulation in their own health behaviors (like PA) can later improve their professional ability to support their patients’ autonomy [12].

Participants must meet all of the following criteria:

Female sexAged between 18 and 25 yearsEnrolled in a Health Sciences degree programProvide written informed consent indicating voluntary participation

Participants will be excluded if they:

Report a current or previous diagnosis of an eating disorder

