Assessments will be conducted at three time points: baseline, immediate post-intervention, and six-month follow-up. To ensure both adherence and intervention fidelity, facilitators will receive prior specific training and follow a structured session guide. Fidelity to the protocol will be monitored by the research team using standardized checklists completed after each workshop. Additionally, a set of retention strategies will be implemented to minimize attrition and missing data, including periodic email reminders and advance notifications of session schedules. Attendance will be systematically monitored throughout the intervention, and participants will be reminded of the importance of continuous participation from the outset to ensure data completeness across all assessment points.

Table 2 presents the standardized pedagogical structure applied in each workshop session, comprising six sequential phases that combine initial welcome, experiential activation, psychoeducational input, group-based activities, individual reflection, and a brief closing synthesis.

**Table 2 pone.0355374.t002:** Standard pedagogical structure of each workshop session.

Session phase	Duration	Description
Welcome and psychological climate	5 min	Facilitators welcome participants, present the objectives of the session, and establish a supportive and non-evaluative group climate
Experiential activation	10 min	Short reflective or experiential activity designed to activate participants’ previous experiences and beliefs related to the workshop topic
Psychoeducational content	15 min	Brief evidence-based explanation of the key concept addressed in the workshop (e.g., motivational regulation, body functionality, social support)
Experiential group activity	20 min	Interactive activities conducted in pairs or small groups allowing participants to apply the concepts through discussion, reflection, or body-awareness exercises
Personal reflection and transfer	5 min	Individual reflection on how the workshop content relates to participants’ own behaviors and experiences
Closing and synthesis	5 min	Summary of key ideas and encouragement to apply the concepts in everyday life

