### Wait-list control condition

Participants assigned to the control group will remain on the wait-list during the intervention and follow-up periods and will not receive any specific intervention. To ensure intervention equity, they will be offered access to the full program upon completion of the T2 assessment.

Participants in both groups will be allowed to continue their usual activities and access external health-related services (e.g., psychological support, personal training, or dietary counseling) throughout the study period. To monitor potential sources of contamination, participants will be asked to report any engagement in such services during the study.

These data will be recorded and considered in the interpretation of the findings. If deemed necessary, additional sensitivity analyses will be conducted to explore the potential impact of external interventions on the study outcomes.

All protocol deviations, including non-adherence to the intervention or engagement in external programs, will be documented and reported following established guidelines for randomized controlled trials.

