No physical risks are anticipated as a result of participation in the intervention. However, given the inclusion of sensitive questionnaires related to body image and eating disorder risk, a participant well-being protocol will be implemented. This protocol includes referral to university psychological support services if risk indicators are identified. No financial compensation will be provided; however, equity will be ensured by offering participants in the control group full access to the intervention program after completion of the follow-up assessment.

The wait-list control design was selected for both methodological and ethical reasons. From an ethical perspective, it ensures that all participants will eventually have access to the intervention, which is particularly relevant in university-based preventive programs targeting body image and motivational processes. Methodologically, this design may enhance participant retention and reduce attrition bias. Moreover, the use of a wait-list rather than an active or minimal-intervention control condition allows clearer detection of intervention-specific effects on perceived autonomy support and motivational regulation.

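### The primary endpoint falls in September 2027, when final-year participants may have left the university, and the article names no provision for reaching them or for giving controls among them the delayed programme

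*Protocol article*

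**What the plan says.** Study and participant timeline gives the calendar: "Participant recruitment is expected to commence in October 2026 and to be completed by December 2026"; "Baseline data collection will be conducted in January 2027"; post-intervention assessment (T1) by March 2027; and, for the six-month follow-up, "data collection is anticipated to take place in September 2027". Primary outcome and Statistical analysis both place the primary endpoint at that last visit.

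Participants' eligibility asks for female sex, age 18-25, consent and being "enrolled in Health Sciences degree programs". The only exclusion is a current or past eating-disorder diagnosis. Recruitment names year of study as an administrative characteristic on which respondents will be compared with the invited population, so several years are expected.

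Experimental intervention describes a set of retention strategies, "including periodic email reminders and advance notifications of session schedules". Administration procedure states that all assessments are digital.

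On the wait-list, the control section says of controls that "they will be offered access to the full program upon completion of the T2 assessment". Ethics and dissemination defends the design on the ground that "it ensures that all participants will eventually have access to the intervention", and adds that it may help retention. The programme itself is face-to-face, on the university's premises.

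**The concern.** Between T1 in March and T2 in September an academic year probably ends. A participant in her final year at baseline may then no longer be a student, read university e-mail or come to campus. The article does not say how such participants will be followed, and its attrition figure does not mention graduation.

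Two things are at stake. First, the primary endpoint is exposed to non-response that follows a known baseline variable. The primary model has group, time, their interaction and baseline outcome as fixed effects, but not year of study. If year predicts both dropout and motivation, missing at random given that model is less plausible than it need be. Second, the ethical case for the wait-list is put as a guarantee. For a control who has left, a campus workshop series offered after September 2027 may be out of reach, and the retention benefit credited to the wait-list would be weak for her.

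**Working it through.** **1. Can final-year students be affected?** Recruitment is October-December 2026, T0 January 2027, T1 by March 2027, T2 September 2027. No eligibility rule refers to year of study. That an academic year ends between T1 and T2 is an inference; the article gives no academic calendar.

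**2. Which named retention tools cover T1 to T2?** Session notices stop being useful when the workshops end, by March. E-mail reminders remain. The article does not say to which address they go.

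**3. The plan's own figures.** For a repeated-measures ANOVA interaction with 2 groups, 3 measurements, f = 0.10 and alpha 0.05, and assuming a within-subject correlation of 0.5 and sphericity (neither is stated in the article):
- noncentrality = f² × N × 3 / (1 − 0.5) = 0.01 × 164 × 3 / 0.5 = 9.84, giving power 0.805 at N = 164 and 0.7998 at N = 162. The stated 164 is reproduced.
- The target of 196 is close to 164 × 1.2 = 196.8. At 20% loss it leaves 196 × 0.8 = 156.8, about 157. It preserves 164 only up to a loss of 1 − 164/196 = 16.3%.

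How the allowance was computed is a separate matter. It matters here only because it leaves no slack for additional loss.

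**4. Number of endpoints exposed.** The documents give neither the final-year share nor the non-response among leavers, so both are assumed.
- Final-year participants: 0.15 × 196 = 29.4 to 0.25 × 196 = 49. The upper value corresponds to four-year degrees with equal uptake by year.
- Missing T2, low end: 29.4 × 0.30 = 8.8, about 9 (8.8/196 = 4.5%).
- Missing T2, high end: 49 × 0.60 = 29.4, about 29 (29.4/196 = 15%).

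**5. Against the allowance.**
- If these losses are already inside the 20%: 0.20 × 196 = 39.2, so they use 8.8/39.2 = 22% to 29.4/39.2 = 75% of it.
- If they come on top, with the same percentages read as extra loss among final-year students who would otherwise have responded: missing = 0.20 + 0.80 × share × extra loss.

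| Share | Extra loss | Missing at T2 | Completers of 196 |
|---|---|---|---|
| any | 0% | 20% | 157 |
| 15% | 30% | 23.6% | 150 |
| 25% | 50% | 30% | 137 |
| 25% | 60% | 32% | 133 |

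For scale, take a two-sided comparison of completers at T2 with equal arms and d = 0.30, the top of the article's simulated range. Power is 0.46 with no baseline correlation and 0.58 with an assumed correlation of 0.5 at 20% missing. At 30% missing it is 0.42 and 0.52.

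**6. The wait-list statements side by side.** Ethics and dissemination speaks of ensured access for all. The control section offers access only after T2. Experimental intervention makes the programme face-to-face. After September 2027 the timeline lists only analysis and dissemination, in October-November 2027. Taken together, access is offered to every control but not secured for one who has left.

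**The case against.** The best reply is that leaving campus is not leaving the trial. T2 is a self-administered digital questionnaire and nothing requires attendance. A reader might infer from the dates that the primary endpoint will be lost in final-year students; the documents do not support that, and this objection stands.

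A reader might also infer that loss will differ by arm, because the delayed programme is worth little to graduated controls. That is not shown either. The intervention arm has no post-T2 incentive at all, so on this factor a worthless offer makes the arms more alike. Year of study is fixed before randomisation, so final-year students are split between arms by chance. Loss driven by year alone would mainly cost precision and generalisability, and the mixed model uses the T1 data of those who miss T2.

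Third, the retention list is introduced as non-exhaustive, and the fields of the registration form are not shown, so a personal contact may already be collected. Likewise, delivery of the programme after the trial is something a condensed article can leave out, so the lack of a slot in the timeline is not in itself a contradiction. Both points are fair.

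What remains is that the article states an open eligibility rule, a September endpoint and a guarantee of access without connecting them.

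**Conclusion.** The point holds as a raised, year-related risk of non-response at the primary endpoint, and as an overstated assurance about the wait-list. Under the assumed shares and non-response rates, 9 to 29 of 196 primary endpoints (about 4-15%) are exposed. If the loss is additional to the planned 20%, power at d = 0.30 falls by about 4 to 6 percentage points in the 30%-missing case. It would be wrong to say that the 20% allowance is breached, since the article does not show whether graduation is already counted in it. The conclusion rests on an academic year ending between March and September 2027, which the calendar makes likely but the article does not state, and on two rates that it does not give. This is a low-cost improvement, still open because recruitment has not begun, and not a flaw that invalidates the randomised comparison.

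**What to change.** 1. At consent, before randomisation, collect a lasting personal (non-university) e-mail or phone number, and send the T2 link and reminders there. If this is already done, say so.
2. Add year of study, already treated as available under Recruitment, as a pre-specified covariate in the primary mixed model, so that missing at random is more plausible if year predicts dropout.
3. State whether the attrition figure of about 20% includes participants who graduate before T2.
4. In Ethics and dissemination, replace the assurance of access for all with an offer of access, or state when and how controls who have left the university can take the face-to-face programme.

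Restricting eligibility by year should not be the main remedy: it would shrink the invited population and narrow generalisability in a trial already confined to one university.

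The cost is one contact field, one model term and a few sentences of text.

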**Fig 1 pone.0355374.g001:**
[figure not shown]
Participant timeline: Schedule of enrollment, interventions, and assessments. ^a^ Timepoints correspond to baseline (T0), immediate post‑intervention (T1), and six‑month follow‑up (T2). No additional time windows are required because all assessments are scheduled within fixed, predefined periods. ^b^ The intervention is delivered across six structured weekly group workshops; therefore, the arrow does not indicate uninterrupted delivery but rather a multi‑session structured psychoeducational program. ^c^ The control group does not receive any active intervention during the trial period and will be offered access to the full program only after completing the follow‑up assessments at T2.

## Discussion

This study protocol outlines a randomized controlled trial evaluating a psychoeducational intervention that integrates Self-Determination Theory (SDT) principles and functionality-oriented body image strategies to promote autonomous PA engagement and psychological well-being among female university students. By addressing motivational quality, PA behavior, and psychosocial risk factors concurrently, the intervention targets mechanisms identified as central to sustainable behavior change and ED prevention [13,19].

The urgency of developing preventive interventions in this population is supported by epidemiological evidence. In Spain, the point prevalence of EDs among young women has been estimated at 7.8% [5]. Using the “iceberg metaphor,” these authors highlight that the observable eating behaviors represent only the visible portion of a deeper psychological process characterized by body dissatisfaction and personal disqualification. Within this context, the university environment represents a particularly valuable setting for prevention because it provides a communal and academic atmosphere where health promotion programs can be integrated into students’ educational experiences [36]. Consequently, interventions delivered in university contexts may offer an efficient strategy to address early psychosocial risk factors associated with disordered eating and maladaptive exercise behaviors.

The relevance of this approach is further supported by prior evidence demonstrating that SDT‑based interventions can produce small‑to‑moderate improvements in perceived autonomy support, autonomy, competence, and motivation [14]. Comparable patterns have been observed in organized PA settings, where satisfaction of basic psychological needs predicts greater enjoyment, persistence, and adaptive regulatory profiles [27]. Similarly, research in educational contexts shows that autonomy‑supportive strategies yield larger effects on motivational quality, underscoring the value of integrating multiple need‑supportive techniques within complex interventions [23]. Collectively, these findings reinforce the theoretical and practical justification for a SDT-informed program such as the one outlined in this protocol. Within this framework, improvements in PA engagement are expected to occur through increased satisfaction of psychological needs and the progressive internalization of exercise-related motives. In line with the proposed mediation hypothesis, autonomous motivation may function as a key psychological mechanism linking need-supportive intervention components with improvements in PA engagement and related health outcomes.

A major strength of the protocol is its strong and explicit theoretical grounding. SDT provides a comprehensive framework for understanding how the satisfaction of autonomy, competence, and relatedness needs fosters higher-quality motivation and adaptive behavioral regulation [10,11]. The intervention incorporates several motivation and behavior change techniques identified through expert consensus, including autonomy‑supportive communication, the provision of meaningful rationales, opportunities for individual choice, competence‑enhancing activities, and the creation of supportive social climates [13], ensuring that the intervention is grounded in clearly identifiable active ingredients. These components are delivered within structured group workshops designed to elicit experiential reflection, promote volitional goal-setting, and cultivate a non-evaluative social context, factors shown to enhance need satisfaction and autonomous motivation in health contexts [14,15].

A distinctive contribution of this trial is the integration of functionality-oriented body image content. Functionality-focused interventions shift attention from appearance to bodily capabilities, fostering more adaptive self-perception and reducing risk factors associated with EDs [16–18]. This approach is theoretically synergistic with SDT because functionality appreciation promotes intrinsic values, self-compassion, and personal meaning—core drivers of autonomous motivation. Moreover, by reducing appearance-based exercise motives, the intervention may help prevent maladaptive patterns such as compulsive exercise or guilt-driven activity [8,9].

Methodologically, the study incorporates several features that enhance rigor, transparency, and reproducibility. The randomized controlled design with a control group aligns with SPIRIT 2025 guidelines, while analyst blinding reduces bias—a procedure rarely implemented in SDT-based trials [14,15]. The measurement battery includes validated Spanish instruments with strong psychometric properties—BPNSFS, BREQ-3, IPAQ-SF, BAS-2, and EAT‑26—ensuring reliable assessment of motivational, behavioral, and psychological constructs [26,28–30,32]. In particular, the use of the BPNSFS allows the examination of both need satisfaction and need frustration, enabling exploration of the “bright and dark paths” of psychological functioning within the SDT framework [28]. Intervention fidelity is supported through facilitator training, session guides, and structured checklists, enhancing the replicability of the program. Together, these procedures aim to strengthen internal validity while facilitating transparency and reproducibility of the intervention design.

Nevertheless, certain limitations should be acknowledged. Conducting the trial within a single university may restrict generalizability to other cultural or institutional contexts, particularly given known differences in PA norms and body image constructs across cultures [28,30]. Blinding of participants and facilitators is not feasible, common in educational and psychosocial interventions, which may introduce social desirability bias [6,15]. The use of self-report measures poses additional challenges: IPAQ-SF may overestimate vigorous PA [29], while the EAT‑26 identifies risk but does not provide diagnostic classification [32]. Finally, although the six-month follow-up assesses medium-term maintenance, longer-term evaluations would be necessary to examine deeper internalization processes and the stability of motivational regulation over time [16]. Because all eligible students are invited (census invitation), self-selection operates at the response rather than the invitation stage: who respond may already be more motivated, which threatens external validity (generalisability) more than the internal validity of the randomised comparison. Rather than merely acknowledging this, the response rate is reported, respondents are compared with the full eligible population, and a post-stratification / inverse-probability-of-response weighting sensitivity analysis probes the robustness of estimates to volunteer bias [37,38]. Residual selection on unobserved characteristics (e.g., baseline motivation) cannot be fully excluded.

Beyond these limitations, this protocol also contributes to ongoing theoretical discussions within SDT research. While the present study focuses on the roles of need satisfaction and need frustration, emerging conceptual work has proposed the additional construct of “need unfulfillment,” describing situations in which psychological needs are neglected rather than actively thwarted [39]. Future research could extend the present design to examine how these distinct need states influence motivational processes in physical activity contexts.

Despite these limitations, the present trial has the potential to make meaningful contributions. If effective, it may offer a scalable, theory-driven model for promoting sustainable PA engagement and positive body image in young women, a group affected by appearance pressures and ED risk [5,7].

Additionally, targeting Health Sciences students has strategic value: improving their autonomous regulation may foster autonomy-supportive communication styles in their future clinical practice, contributing to more person-centered healthcare [10,12]. The treatment of personal data will strictly comply with [33], ensuring the reconciliation of the right to data protection with the freedom of scientific research. Planned dissemination through peer-reviewed publications, conference presentations, and institutional reports will ensure that the findings contribute to both scientific knowledge and the development of theory-informed health promotion strategies in university and healthcare settings.
